# Working memory training in children with neuropsychiatric disorders and mild to borderline intellectual functioning, the role of coaching; a double-blind randomized controlled trial

**DOI:** 10.1186/s12888-017-1274-6

**Published:** 2017-03-28

**Keywords:** Mild to borderline intellectual functioning, ADHD, ASD, Working memory training, Coaching, Randomized controlled trial

## Abstract

**Background:**

Working memory training (WMT) has been shown to offer therapeutic benefits to both patients with Attention-Deficit Hyperactivity Disorder (ADHD) and patients with mild to borderline Intellectual Disabilities (MBID; 60 < IQ < 85). However, robust evidence for transfer effects and treatment benefits of WMT over placebo training are lacking. Owing to the nature of double-blind research designs in RCTs, children have received non-specific coaching not based on their actual training performance. Active coaching based on individual training results (such as in clinical practice) might enhance the efficacy of Cogmed WMT. Furthermore, clinical experience and the general treatment approach to these vulnerable children has shown that the intensity and duration of WMT is often too stressful. This study therefore investigated the efficacy of a less intensive, but more prolonged Cogmed WMT (including active personalized coaching and feedback) in reducing behavioral symptoms and improving neurocognitive functioning and academic achievements in children with MBID and neuropsychiatric disorders.

**Methods/design:**

A double-blind RCT with children (age 10.0–13.11) with neuropsychiatric disorders (ADHD and/or autism spectrum disorder (ASD)) and MBID (IQ: 60 < IQ < 85). Two groups (each *n* = 26) will receive Cogmed WMT (version R/M) at home or at school for 8 weeks, 4 days a week, at 30 min a day. One group will receive active personalized coaching and feedback based on their actual individual performance during Cogmed training**.** The other group will only receive general non-personalized coaching (i.e. no receive personalized coaching and feedback). Both groups will undergo a neurocognitive assessment (working memory, executive functioning, academic achievements) before and after training and complete several questionnaires (behavioral problems, parenting style) with a 6 months follow-up.

**Discussion:**

This study will add to the literature since the role of coaching in Cogmed WMT has not been studied before. It will also provide opportunities to investigate an alternative version of WMT in a large group of vulnerable children, for whom few evidence-based treatments are available. Ultimately, this will allow us to advise mental health care professionals and special education schools about the use of this type of intervention for children with MBID and neuropsychiatric disorders.

**Trial registration:**

Dutch Trial Register. NTR5223. Registration date 06–09-2015.

## Background

It is important to develop evidence-based treatments for children with MBID (IQ: 60 < IQ < 85) and neuropsychiatric disorders, as regular cognitive-behavioral therapies are often too complex for this group due to lower intellectual abilities and less developed adaptive skills. The group of children with MBID is of particular interest, since 33% may have a comorbid psychiatric disorder, the most common being ADHD and ASD [1].

WMT has been shown in several studies to offer therapeutic benefits to both patients with ADHD and patients with MBID. Recent reviews on the efficacy of Cogmed WMT have suggested Cogmed RM may be a potentially efficacious treatment for ADHD [2, 3]. Studies on the MBID-group report improvements in short-term memory (STM) and working memory (WM) as well as in academic achievements [4, 5]. A recent meta-analytic review revealed a significant overall pretest-posttest effect size for WMT for individuals with intellectual disabilities compared to controls [6]. On the other hand, 2 previous meta-analyses on non-pharmacological interventions suggest better evidence for the efficacy of cognitive training is required before these interventions may be labelled as effective interventions for ADHD [7, 8]. Rapport and colleagues [9] showed moderate improvements in STM performance in a meta-analysis of several cognitive training programs in children with ADHD when focusing on STM alone (such as Cogmed WMT). However distal transfer effects as well as training effects on other neurocognitive domains, academic achievements or behavior were negligible [9].

Extended research on the efficacy of WMT in a variety of patient groups is needed. This study is designed to examine the effect of WMT in a scientific rigorously way in children with MBID and neuropsychiatric disorders (i.e. ADHD, ASD). Previous studies on Cogmed WMT have underlined the importance of active, personalized coaching and feedback during training [3, 10]. A study by van Dongen and colleagues [10] included a younger ADHD patient group with normal intelligence. Both children treated with Cogmed and those treated with the placebo control version improved on the outcome measures. Due to the inclusion of a placebo-controlled version, children received non-personalized coaching (not based on their actual training performance). This is not consistent with the personalized coaching and feedback (based on actual performance) in clinical practice. Preliminary blind analysis from our recent study on the efficacy of Cogmed in neuropsychiatric disorders and borderline intellectual functioning ([name], [name], [name], [name]. Working memory training in children with neuropsychiatric disorders and borderline intellectual fucntioning; a randomized controlled trial, unpublished raw data) has also shown that both groups, i.e. those children treated with Cogmed and those treated with the placebo control version of Cogmed, improved significantly on various variables. It is probable that active personalized performance coaching in the active Cogmed group during the training period could have made the difference in performance between the 2 groups.

A different explanation for the progression in both groups in our recent study may be that this control version of Cogmed WMT is already challenging enough for children with intellectual disabilities. The WM load in this version has a maximum of 3 items which may place a high demand on the WM capacity of children with MBID. This group may, on average, have a baseline WM capacity below 3, which makes the control version questionable for the MBID-group. This low baseline may also increase the daily duration of the training and consequently decrease the participating children’s motivation. Training is, in general, more difficult for this population. A recent pilot study indicated that protocols containing more training days with shorter training durations per day, may lead to similar or even better training effects compared to the standard protocol, even with less total training time [11]. This is consistent with the general treatment approach for children with MBID. These children may have a shorter attention span and need longer treatment durations before effects – which last for a longer period of time are noticeable [12]. Therefore, based on clinical experience and previous research, a less intensive (i.e. 4 instead of 5 days per week and 5 instead of 8 exercises per day) and more prolonged (i.e. 8 instead of 5 weeks in a row) WMT would probably better fit children with MBID and neuropsychiatric disorders.

In conclusion, robust evidence for transfer effects and treatment benefits of WMT over placebo training are lacking. Double-blind research designs in randomized controlled trials, in which children receive non-specific coaching not based on their actual training performance, might play a crucial role in these findings. Active coaching based on individual training results (comparable to clinical practice) might enhance the efficacy of Cogmed WMT. Furthermore, based on clinical experience and the general treatment approach to children with MBID and neuropsychiatric disorders, it is our opinion that the intensity and duration of WMT is often too stressful. Therefore, this study will examine the efficacy of a less intensive and more prolonged Cogmed WMT in these vulnerable children. Secondly, the potential benefits of active, personalized coaching and feedback during the Cogmed WMT in terms of reducing behavioral symptoms and improving neurocognitive functioning and academic achievements in children with MBID and neuropsychiatric disorders will also be studied.

### Aims

The overall purpose of the study is to gain insight into Cogmed WMT, and in particular to identify which elements may help to develop individually tailored effective treatment possibilities for groups of vulnerable children.

The primary aim of this study is to investigate the efficacy of a less intensive but prolonged Cogmed RM WMT with active personalized coaching and feedback in children with MBID and neuropsychiatric disorders, compared to a less intensive but prolonged RM Cogmed WMT without personalized (i.e. only general non-personalized) coaching and feedback, on neurocognitive functioning as measured with the backward block recall task.Secondly, the efficacy of active personalized coaching will be investigated on various other neurocognitive functioning domains (WM and executive functioning), academic achievements (arithmetic and reading), behavioral problems and parenting style.

It is hypothesized that participants who receive a less intensive but prolonged RM Cogmed WMT with active personalized coaching and feedback demonstrate greater improvement on neurocognitive functioning, academic achievements, behavioral problems and parenting style, directly after training and 6-months post baseline, compared to those who receive a less intensive but prolonged RM Cogmed WMT with only general non-personalized coaching and feedback.

## Methods

### Approval

The ethics approval was obtained from the Medical Ethical Committee (NL52647.091.15/METC2015–1618) at Radboud Academic Medical Centre in Nijmegen, the Netherlands.

### Design

Two groups of 26 children will train 8 weeks, 4 days a week for an average of 30 min (5 exercises) each day in a double-blind randomized controlled trial. Parents, children and teachers will be blinded for the group allocation, i.e. 1. personalized coaching and feedback or 2. non-personalized feedback and general coaching. All participants will undergo a behavioral and neurocognitive assessment including academic achievement measures (pre- and post- assessment). The post-assessment will be carried out in the week after the last session, and an evaluation of the training will take place. In this evaluation parents are questioned about their positive and negative experiences with the training. Furthermore they are asked if they would recommend the training to others and to grade their contentment with the training between 0 (very poor) and 10 (very good). Six months after the last training session there will be a follow-up. Selection of participants, screening for eligibility and assessments will be performed at Karakter, Centre for child and adolescent psychiatry. The training will be done at home and/or at school.One group will be treated with a less intensive but more prolonged version of the Cogmed WMT, version R/M. They will receive personalized coaching and feedback (5 sessions) based on their actual performance during the training;One group will be treated with a less intensive but more prolonged version of the Cogmed WMT, version R/M. They will receive the same amount of coaching time, but without personalized feedback (only non-personalized coaching).

### Setting

Two different types of schools (primary- and secondary special education) in the area of Arnhem/Nijmegen, the Netherlands will be contacted for participation in this study.

### Recruitment

Recruitment will take place among referrals and patients of Karakter child and adolescent psychiatry in the Netherlands. Parents and children will receive detailed written information about the study. If they have any questions about the study, they can call one of the investigators. In addition, participants will be recruited through the Dutch national association for parents of children with developmental disorders (i.e. Stichting Balans). Participants will be recruited through advertisements on the association’s website and magazines. Lastly, participants will be recruited among children visiting special education classes. Primary education school boards will be contacted for participation. If permitted by school board an advertisement will be placed on the school’s website and in the school magazine. The advertisement will be clear about the study objective and design as well as the benefits and the risks of participating in the study. The investigators will only contact parents after they have given permission to their therapist or school board to be informed about the research. Training will be started after signed informed consent has been obtained from both parents and the child (age ≥ 12 years). When informed consent is received by the research team, the investigator will inform the general practitioner and the involved therapist/psychiatrist about the participation.

### Inclusion and exclusion criteria

#### Inclusion

Children participating in this study will be aged between 10 years 0 months and 13 years 11 months with an IQ score between 60 and 85 (mild to borderline intelligence level). They will have been classified with a neuropsychiatric disorder, i.e. ADHD and/or ASD in line with DSM-IV/DSM-5 [13, 14]. Children with comorbid Oppositional Defiant Disorder (ODD) will also be included. Access to a PC with Windows Vista or Windows XP with an internet connection and speakers at home or at school will be required for the training. Children on medication will only be included if there is “room for improvement of the ADHD symptoms” and medication dosages remain stable during study participation.

#### Exclusion

Exclusion criteria are (1) treatment at an inpatient or day treatment clinic, (2) regular use of other medication than for ADHD, (3) psychiatric diagnoses other than ADHD, ASD or ODD, (4) neurological disorders (e.g. epilepsy) in the last 2 years, (5) current or a history of cardiovascular disease, (6) severe motor and/or visual impairment, (7), current participation in another clinical trial, (8) insufficient motivation or time to pursue training (child, parent(s), or aid(es) are too busy or not motivated to participate), (9) medical illness requiring medical treatment.

#### Randomization

Randomization will be used: 1. to avoid bias in the assignment of participants to treatment. 2. to increase the likelihood that known and unknown factors (expectations of the therapy, motivation etc.) are evenly balanced across treatment groups and, 3. to enhance the validity of statistical comparisons across treatment groups. Randomization will be done by an independent person not involved in this research project, and will be provided through sealed envelopes.

Four strata will be constructed based on sex and diagnosis, to enable important prognostic characteristics (the stratification factors) to be balanced between the treatment groups. A block randomization schedule with varying block sizes will be performed separately within each stratum to reduce the possibility of selection bias. By using this method, we will have the most optimally balanced allocation of participants possible among treatment groups. In addition to this the use of varying block sizes will increase the randomness of the group allocation.

Professionals involved with the pre-, post and follow-up assessment will not be informed about the coaching method. Professionals involved in the coaching will not be involved in the pre- post and follow-up assessment. Parents, aides and children will be informed about the weekly contact with their coach by telephone, but will not be informed about coaching-content specifics beforehand. Reason for breaking the blind is that information is important for medical management of the subject. Appropriate documentation will be completed, signed and dated by the investigator with the reason for breaking the code. Participants will be informed about the allocated intervention after the post-treatment assessment.

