### Sample size

Data from Fuchs and Fuchs [28] and Wickes [29] were used for the population estimates. In this first meta-analysis the effects of examiner familiarity on children’s test performance was examined. The data for the meta-analysis came from 22 controlled studies involving 1489 subjects. In the typical study, the effect of examiner familiarity raised test performance by .28 standard deviations. Differential performance favoring the familiar examiner condition was greater when subjects were of low socioeconomic status (SES), were tested on comparatively difficult tests, and knew the examiner for a relatively long duration. The second study tested the general hypothesis that test results will be modified by those aspects of the testing situation which are sometimes not carefully controlled or are treated as if they were unimportant. Thirty-six male subjects in two experimental groups and one control group were used to study the effects of perfunctory verbal comments and nonverbal actions on test results. The findings of the study suggest that such comments as ‘Good’ or ‘Fine’ and such actions as smiling and nodding by examiners have a decided effect upon test results. These data is used as population estimates when comparing the effect of active coaching and personalized feedback versus general non-personalized coaching in Cogmed RM WMT. With a sample size of 50 participants (25 per group), our trial will have 79% power to find an effectsize of .40 between groups and a power of 93% to find an effectsize of .50, when co-variating for WM performance at baseline level. An unpublished study in a similar patient group ([name], [name], [name], [name]. Working memory training in children with neuropsychiatric disorders and borderline intellectual fucntioning; a randomized controlled trial, unpublished raw data) has shown that four (5%) out 76 participants dropped out of the study. Therefore we will include 2 extra participants in this second intervention study. In total, 52 participants (26 per group) will be included.

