### Statistical analysis

Statistical analyses of all data will be undertaken using the SPSS statistical program (SPSS 21.0). Descriptive statistics will be reported for each variable of interest for the two groups (active coaching versus general non-personalized coaching). First univariate analyses will be carried out. An independent-samples t-test will be run to determine if there are differences in age, IQ or severity of ADHD or ASD symptoms (measured with the VISK or AVL questionnaire) between the two groups. A chi-square test will be used to examine whether there is an association between gender, use of medication, whether the intervention occurred in a subject’s home or school and the group (active coaching versus general non-personalized coaching).

The mean, standard error (SE) and 95% confidence intervals will be computed for each parameter. For the primary analyses, an analysis-of-variance (ANOVA) will be conducted on the backward block recall task with group (2 levels) as the between-subject factor and time (pre-, post and follow-up assessment) as the within-subject factor. The group by time interaction will show the treatment effect (*p < 0.05).* For the secondary analyses, a multivariate ANOVA (MANOVA) will be conducted on the other neurocognitive, academic and behavioral scales with again group (2 levels) as the between-subject factor and time (pre, post and follow-up assessment) as the within-subject factor. The group by time interaction will reveal the treatment effect on these variables (*p < 0.05).* In case of withdrawal, discontinuation or missing data (if patients have been missed for any reason (i.e. illness) more than 5 training sessions), intention to treat analyses will be performed.

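### Sex and diagnosis define the randomisation strata but are left out of the primary and secondary models, which loses precision if they predict change over time

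*Protocol article*

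**What the plan says.** Protocol article, Randomization: "Four strata will be constructed based on sex and diagnosis". The stated purpose is "to enable important prognostic characteristics (the stratification factors) to be balanced between the treatment groups". The mechanism follows: "A block randomization schedule with varying block sizes will be performed separately within each stratum". Block sizes are not given.

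Protocol article, Statistical analysis: the primary ANOVA on backward block recall is run "with group (2 levels) as the between-subject factor and time (pre-, post and follow-up assessment) as the within-subject factor", and "The group by time interaction will show the treatment effect", at a 0.05 level. The MANOVA for the other scales has the same two factors. Sex appears in this section only in a chi-square comparison of the groups. Neither sex nor diagnosis is in a treatment model.

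Protocol article, Sample size: "With a sample size of 50 participants (25 per group), our trial will have 79% power to find an effectsize of .40 between groups". The same sentence gives 93% power for .50 and says that baseline working memory is adjusted for.

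**The concern.** Blocking on a factor that predicts the tested contrast lowers the true variance of the group difference, because the arms are balanced on that factor. A model without the factor leaves its variance in the error term, so the reported standard error exceeds the true one. The test is then conservative, the confidence interval too wide, and some of the power bought by stratifying is lost. With 25 children per group analysed and a stated power of 79%, there is little to spare. The article itself describes the two factors as prognostic, which is the usual reason for keeping them in the analysis.

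**Working it through.** **1. The plan's own power figure.** Inputs: 25 per group and effect sizes .40 and .50 (Sample size section); two-sided alpha 0.05 (the level is stated, two-sidedness is assumed).

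- Read as Cohen's f, .40 is a standardised difference d = 2 × .40 = 0.80. The noncentrality is 0.80 × √(25/2) = 2.83. With one degree of freedom used for the baseline covariate, power is 79.1%.
- In the same way, .50 gives d = 1.00 and power 93.4%.
- Both match the stated 79% and 93%. Read as d with no gain from the covariate, .40 gives only 28%. As d it reproduces only with an unstated baseline correlation of about 0.86.

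The rest uses d = 0.80, the value at which the stated 79% holds.

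**2. What the planned test removes.** Write a child's score as stable stratum effect + stratum-specific change + group effect + error. In post minus pre, the stable stratum effect subtracts out and the stratum-specific change stays. The quantity that matters is therefore R², the share of the variance of *change* explained by the strata. The article does not give it. The range assumed here is 0 to 0.20.

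**3. Closed form with perfect balance within strata.** The excess in the standard error is 1/√(1 − R²) − 1. The true type I error of the unadjusted test is 2 × [1 − Φ(1.96/√(1 − R²))].

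- R² = 0.05: 2.6% and 4.4%
- R² = 0.10: 5.4% and 3.9%
- R² = 0.20: 11.8% and 2.8%

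**4. Simulation with realistic balance.** Blocks left incomplete when recruitment ends make real balance less than perfect. Stratified block randomisation was simulated with N = 50, strata shares of 40/30/18/12% and blocks of 2 and 4 (shares and block sizes assumed), with up to 6,000 null runs and 3,000 runs at d = 0.80. It used a single change contrast, a simplification of the three-assessment interaction. The standard-error ratio and type I error come from the null runs.

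| R² of change | Unadjusted SE / true SE | Type I error, unadjusted | Power, unadjusted | Power, adjusted |
|---|---|---|---|---|
| 0, strata predict nothing | 0.98 | 5.6% | 79.7% | 79.4% |
| 0, strata explain 20% of level | 0.97 | 5.6% | 79.5% | 79.1% |
| 0.05 | 1.03 | 4.5% | 79.3% | 80.2% |
| 0.10 | 1.05 | 4.0% | 80.6% | 83.5% |
| 0.20 | 1.09 | 3.6% | 80.6% | 86.5% |

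The first two rows are Monte Carlo noise around 1.00 and 5%. At R² = 0.20 the ratio was 1.09 in the null runs and 1.11 in the runs with an effect. With the strata in the model, the null-run ratio was 0.97 to 1.00 and type I error 4.6 to 5.7%.

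**5. Level against change.** In the second row, an unadjusted between-group comparison of *level* would have a standard error 12% too large and a type I error of 2.6%. That is not the planned test. The planned contrast shows no excess.

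**6. Cost of adjusting.** Three extra degrees of freedom with R² = 0 move the calculated power from 79.1% to 79.0%. In the repeated-measures form, the within-subject error degrees of freedom go from (50 − 2) × 2 = 96 to (50 − 5) × 2 = 90.

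**The case against.** The strongest reply is that the planned test is a within-subject contrast. Being prognostic for level is not enough, and nothing in the article says that sex or diagnosis predicts change in backward block recall. This stands. A reader might infer from the omission alone that the standard errors are too wide. The documents do not support that: with strata that explain level only, the standard error is right and adjustment gains nothing.

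A second reply is that the unadjusted test stays valid, so this is an efficiency matter. This also stands and limits the weight of the point.

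A third reply is that a condensed article may leave model detail to a fuller document. It does not answer the main point, because the article names the outcome, both model factors, the term tested and the significance level. It does answer another inference. Eligibility is "i.e. ADHD and/or ASD in line with DSM-IV/DSM-5", so a reader might count three diagnostic groups, conclude that there should be six strata, and think that children with both diagnoses have none. With diagnosis coded in two levels, for example ASD present or absent, 2 × 2 = 4 and every child has a stratum. The article does not list the levels, and that is detail it may fairly leave out.

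Finally, the remedy takes slightly more than one extra main effect, because the time interactions are needed.

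**Conclusion.** The mismatch between randomisation and analysis is explicit and worth correcting, but its consequence is conditional. If the strata explain 5, 10 or 20% of the variance of change, the unadjusted standard error is about 3, 5 or 9% too large, type I error is about 4.5, 4.0 or 3.6%, and the power forgone is 0.9, 2.9 or 5.9 points (adjusted minus unadjusted power in the table). At 0% there is no loss. The 9% is a simulation result; the perfect-balance limit is 12%.

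These sizes rest on the assumed R², strata shares and block sizes, on d = 0.80, and on one change contrast standing in for the three-assessment interaction. The direction does not depend on them: the present analysis is at worst conservative. Nothing here implies bias, an inflated false-positive rate or an invalid trial.

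**What to change.** Add the randomisation strata to the primary model and to every secondary model, coded exactly as in the randomisation list. There are two equivalent routes:

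- In the repeated-measures ANOVA and MANOVA, enter sex and diagnosis together with their interactions with time. Main effects alone do not touch the error term of the group by time test.
- In an ANCOVA of the post-training or follow-up score on group and baseline, enter sex and diagnosis as covariates. This form also fits the baseline adjustment that the Sample size section assumes.

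The cost is 2 degrees of freedom for the two main effects, or 3 for the four strata, and about 0.1 power point if the strata predict nothing. Both variables are known at randomisation, so no further data or children are needed. The change should be recorded before the allocation is linked to outcomes.

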## Discussion

It is of great importance to undertake a treatment-efficacy study in this large vulnerable population of children with MBID and co-occurring psychiatric disorders. Evidence-based treatment possibilities are scarce for these children, since they are often excluded from participation in scientific research due to the heterogeneity of the population. If a less intensive but more prolonged version of the Cogmed WMT intervention with active coaching and feedback appears to improve neurocognitive functioning, academic achievements and/or behavioral problems, it can be implemented in mental health care and special education schools as an evidence-based intervention for children with MBID and neuropsychiatric disorders. Our study also adds to the literature in that this will be the first study to compare effects of different types of coaching. This aspect is of great value, since several studies have shown significant improvements on both the WM condition as well as the placebo condition if coaching is not personalized. Furthermore, a less intensive and more prolonged WMT would probably better fit these children and might result in an increased training benefit and less dropout. On the other hand one could argue that 4 training sessions a week, for a period of 8 weeks, with a shorter duration of training time a day, is indeed less intensive than 5 training sessions a week, for a period of 5 weeks, with a longer duration of training time a day.

Finally, one strength of this study is the double-blind randomized controlled design, which is the most robust design in trials attempting to establish efficacy. This design not only takes into account near transfer effects, but also far transfer effects. These effects are measured up to 6 months after training.

In this study, the second (non-personalized) coaching condition might be a challenge in clinical practice. Coaches should not be tempted to give any substantive feedback to the parent on how to motivate their child when training difficulties occur. On the other hand, a greater degree of training dropout might take place when non-personalized coaching is performed more rigidly. One limitation of this study is the use of single tasks to assess the generalization effects of WMT. It remains unclear whether any improved performance will be due to an acquired underlying ability and/or reflect practice effects. Therefore the results may have to be interpreted cautiously.

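### Families may be told their allocation before the T3 follow-up that enters the primary group-by-time test, which leaves only assessor blinding planned at T3

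*Protocol article*

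**What the plan says.** Design defines who is blind: "Parents, children and teachers will be blinded for the group allocation". On timing it says: "The post-assessment will be carried out in the week after the last session" and "Six months after the last training session there will be a follow-up". The footnote to Table 1 labels these points T2 and T3.

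Randomization sets the disclosure rule: "Participants will be informed about the allocated intervention after the post-treatment assessment". The same paragraph keeps the staff who do the baseline, post-training and follow-up assessments uninformed of the coaching method, and keeps coaches out of the assessments. It also allows the code to be broken for medical management.

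Statistical analysis defines the primary ANOVA on backward block recall with "time (pre-, post and follow-up assessment) as the within-subject factor", and states: "The group by time interaction will show the treatment effect". The secondary MANOVA uses the same three time points.

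The Discussion claims that "one strength of this study is the double-blind randomized controlled design", and adds that effects are followed up to 6 months after training.

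**The concern.** The trial compares two kinds of coaching around the same training program. The section on Condition 1 says that the program's developer recommends personalized coaching as the best form of delivery, so learning one's arm is not neutral news. Randomization gives balance in expectations and motivation as a reason to randomize. Disclosure between T2 and T3 can upset that balance before the last measurement.

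Once told, parents rate behavior and parenting at T3 as unblinded raters. Children are tested at T3 knowing which coaching they had. T3 is a level of the time factor, and the treatment effect is read from the interaction over all three time points. A group difference that arises at T3 from expectation alone would therefore count as a treatment effect. Analysis cannot restore the blind afterwards.

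**Working it through.** **1. Order of events.**

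| Event | Time | Section |
|---|---|---|
| Training | 8 weeks | Design |
| T2 | within a week after the last session | Design |
| Disclosure | after the post-treatment assessment, no later limit given | Randomization |
| T3 | 6 months after the last session | Design; Measures and procedures agrees |
| T3, other wording | "directly after training and 6-months post baseline" | Aims |

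Randomization names the baseline, post-training and follow-up assessments separately, so the post-treatment assessment is T2. Under Design, the gap from T2 to T3 is about 6 months. Under Aims, with 6 months taken as about 26 weeks, T3 falls 26 - 8 = 18 weeks after training ends, or about 4 months. Either way T3 follows T2, and no sentence holds disclosure back until T3 is done.

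**2. Which scores are exposed at T3.** Count of secondary scores from Table 1:

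- child tests: 8
- parent ratings: VISK, AVL, BRIEF, APQ = 4
- teacher ratings: VISK, AVL, BRIEF = 3
- total: 8 + 4 + 3 = 15

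The 4 parent ratings come from people covered by the disclosure, because telling a participating family tells the parent. The 3 teacher ratings are uncertain, because the rule names participants and does not mention teachers. The 8 child tests and the primary task are performed by a child who may know the arm, but given by uninformed staff.

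**3. How a T3-only shift would enter the primary test.** The plan gives no figure on this point, so there is none to reproduce. The following is a sensitivity illustration under assumptions that are not in the document: no true effect, equal SD at each time point, compound symmetry with correlation ρ, 25 analyzed per group (from Sample size), and a shift of b SD between groups at T3 only.

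The group differences at T1, T2 and T3 are 0, 0 and b, with mean b/3. The sum of squared deviations is 2 × (b/3)² + (2b/3)² = (2/3)b². The interaction F test has 2 and 2 × 48 = 96 degrees of freedom, with noncentrality

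λ = (25/2) × (2/3)b² / (1 - ρ) = 8.33 b² / (1 - ρ).

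For b = 0.2 and ρ = 0.5, λ = 8.33 × 0.04 / 0.5 = 0.67. For b = 0.2 and ρ = 0.8, λ = 8.33 × 0.04 / 0.2 = 1.67.

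Probability of a significant interaction at nominal 5%:

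| b (SD, assumed) | ρ = 0.5 | ρ = 0.7 | ρ = 0.8 |
|---|---|---|---|
| 0 | 5.0% | 5.0% | 5.0% |
| 0.1 | 6.2% | 7.1% | 8.2% |
| 0.2 | 10.2% | 14.0% | 18.9% |
| 0.3 | 17.4% | 26.6% | 38.2% |

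The table shows how sensitive the test is to such a shift. It does not show that a shift will occur.

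**The case against.** The best defense is that the primary outcome is well protected. Backward block recall is a performance task, given at T3 by staff who are not told the coaching method. Training and all five coaching contacts are over before disclosure, so delivery of treatment cannot be affected. A bias would have to act through the child's effort, through family behavior in the interval, or through a family revealing its arm to the assessor. This stands, and it is why the risk is smaller for the primary task. It does not help the parent ratings, where the rater is the person who has been told.

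The rule could also be met by disclosing after T3, since that too comes after T2. But nothing requires the delay, and the plain reading is disclosure once the post-assessment is done.

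A reader might infer three stronger points that the document does not support:

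- **T3 is wholly unblinded.** It is not, because assessor blinding is planned to continue.
- **All 7 rated scores of the 15 are exposed.** Three of these are teacher ratings, and disclosure to teachers is not stated.
- **The .28 SD in Sample size measures the likely bias, or matches the planned effect.** It is an examiner-familiarity effect from a cited meta-analysis. It says nothing about unblinding, and it is smaller than the .40 and .50 for which power is given.

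**Conclusion.** The point holds in limited form. The participant and parent blind, which Design makes part of the double-blind, is lifted by rule before T3. One of the two post-baseline time points in the primary and secondary group-by-time tests is then protected by assessor blinding alone. The double-blind claim in the Discussion is sound up to T2 but not for the 6-month effects.

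Exposure is clearest for 4 of the 15 secondary scores, uncertain for the 3 teacher scores, and smaller for the primary task and the other child tests. T1-T2 comparisons are untouched. Neither the size nor the direction of a bias can be derived from the document, and the 10-19% figure rests wholly on an assumed 0.2 SD shift and the stated correlation range. The conclusion assumes that the post-treatment assessment means T2 and that telling participants includes their parents. The text supports both.

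**What to change.** Change the sentence in Randomization so that participants, parents and teachers learn the allocation only after the T3 follow-up is completed, apart from the medical unblinding already described. Make the information given to families agree. Reconcile the timing of T3 between Aims and Design, so that the date that releases the allocation is unambiguous.

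If some families have already been told, make the T1-T2 contrast the confirmatory one, report T3 as participant-unblinded, and limit the double-blind claim to T2.

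The cost is a one-sentence amendment and a wait of about four to six months more before families learn their arm. The planned 52 participants and the stated power are unaffected by moving the disclosure date.
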